##### Task initiation delay paradigm (TIDP)

The Task Initiation Delay Paradigm (TIDP) will be used to evaluate participants' readiness for task initiation and their perception of time delay. Stimuli will consist of a green fixation cross (“+”) serving as a preparatory cue and target stimuli represented by the letters “X” or “O.” Three delay conditions will be introduced between the cue and target stimulus: 100 ms, 500 ms, and 2,000 ms. Ten trials will be conducted under each condition in a total of four randomized blocks. Participants will be instructed to respond as quickly as possible by pressing the “F” key when “X” appears and the “J” key when “O” appears. The trial sequence will proceed as follows. A fixation cross will be presented at the center of the screen until participants are prepared. A green cue (“+”) will then appear for 100 ms, followed by a blank screen representing the delay interval (100, 500, or 2,000 ms). After the delay, the target stimulus will appear and remain visible until the participant responds or for a maximum of 2,000 ms. Each trial will be followed by a 500 ms inter-trial interval (ITI). Prior to the formal task, participants will complete 5–10 practice trials to familiarize themselves with the delay conditions and response rules.

**Figure 2 F2:**
[figure not shown]
Task initiation delay paradigm (TIDP) process diagram. It depicts the process of the task initiation delay paradigm. It starts with a fixation point, followed by a delay period (100/500/2,000 ms) with a green cross. Then a target appears (press “s” for “X”, press “j” for “O”), and finally, there is a 500 ms inter-trial interval.

### Healthy control group

The healthy control group will not receive any intervention. Both GPS/PASS scales and ERP (P300, N200) under Go/No-go emotion task and TIDP will be collected at baseline”.

## Outcomes

### Primary outcome

General Procrastination Scale (GPS) will be used as the primary outcome measure. The GPS is one of the most widely used and validated trait procrastination scales and has demonstrated good applicability for Chinese college students. It consists of 20 items scored on a 5-point Likert scale from “strongly disagree” (1 point) to “strongly agree” (5 points), and covers multiple domains including academic activities and activities of daily living (52). Note that higher scores on certain items are indicative of greater procrastination while higher scores on others are indicative of lower procrastination tendency, so some item scores are reversed before summation. After appropriate reversal, a higher total score is indicative of greater procrastination tendency, with a score between 20 and 49 points indicating low, 50–69 moderate, and 70–100 high procrastination. Xue and colleagues reported a Cronbach's α coefficient of 0.807 and a test–retest correlation coefficient of 0.756 after 4 weeks, indicating good internal consistency and reliability (53). Exploratory and confirmatory factor analysis revealed a two-factor structure consisting of active avoidance and lack of planning, and the model fitting effect was good (CFI=0.914, TLI=0.901, RMSEA=0.069, SRMR = 0.072). The GPS was also positively correlated with total scores on the Irrational Procrastination Scale and the Academic Burnout Scale (r = 0.753, 0.677, all *P* < 0.001), supporting good reliability and validity (54).

### Secondary outcomes

The Procrastination Assessment Scale for Students (PASS) was developed by Solomon and Rothblum in 1984 to measure students' academic procrastination behavior, including for coursework, test preparation, and essay writing (55). In the proposed study, the first part of the scale, revised by Hou and Gai (56), will be used as a secondary outcome measure. This section consists of 18 items covering 6 tasks: “writing term papers”, “reviewing exam preparations”, “academic assignments assigned by teachers”, “academic administration tasks”, “attendance assignments”, and “general school activities”. All items are scored on a 5-point Likert scale, and the scores of the first two items related to each of the six tasks are added together to calculate 6 task subscores from 2 to 10. The total score ranges from 12–60 points, with a higher score indicating a higher degree of academic procrastination. A total score >36 indicates problematic academic delay, while a subscore > 6 indicates procrastination on a specific task. In the proposed study, a score of 24 will be defined as severe procrastination. A previous study reported a Cronbach's α coefficient of 0.82 and test–retest coefficient of 0.78 after 2 weeks, indicating good internal consistency and reliability. Exploratory and confirmatory factor analysis demonstrated a three-factor structure, and model fitting was good (CFI = 0.921, TLI = 0.912, RMSEA = 0.071, SRMR = 0.068). Further, Yip and colleagues reported that the PASS score was significantly correlated with both the GPS score and academic performance (*r* = 0.65, 0.45, all *P*% 3C0.001), supporting good construct validity (55).

### Adverse events

Adverse events that may occur during acupuncture include broken, syncope, local hematoma, infection, and abscess, while post-acupuncture discomforts may include residual acupoint site pain, nausea, vomiting, palpitations, dizziness, headache, anorexia, and insomnia. Timely recording of these events is critical to enhance participant safety. In the proposed study, the incidence rates and average frequencies of these events will be recoded on a specific form for review and appropriate follow-up (Figure 3).

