#### Dropout criteria

In addition, we will preset dropout criteria as follows:

Mistaken admission (subsequently found not to meet one or more inclusion criteria or found to meet one or more exclusion criteria);Poor compliance or voluntary withdrawal;Onset of treatments prohibited by this protocol, or changing treatment methods during the program;Serious adverse reactions to the interventions.

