##### Dropped cases will be handled as follows:

After drop out, the attending doctor will try to contact the subject by phone or letter to obtain the reason(s) and schedule a final visit if possible to complete the assessable items.For cases that quit the trial due to adverse reactions or ineffective treatment, the attending doctor will take appropriate measures in accordance with current treatment guidelines.The “Summary of Treatment Completion” and “Clinical Trial Completion” in the CRF will be filled in.All excluded and dropped cases will be included in the intention-to-treat analysis after the trial ends.

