#### Running group

The running group will perform moderate-intensity continuous training (MICT) according to American College of Sports Medicine (ACSM) guidelines with precise exercise intensity control according to heart rate reserve (HRR) calculations. Maximum heart rate (HRmax) and anaerobic threshold heart rate (ATHR) will be measured for each participant at baseline using a standard treadmill escalating load test (Bruce protocol), and HRR calculated as HRR = HRmax-Resting Heart Rate (RHR). Training intensity will be maintained in the 60–75% HRR range (equivalent to 70–85% of maximum heart rate) by real-time monitoring using a wearable heart rate monitor. Participants will run 3 times per week for 30 min, including 5 min of brisk warm-up walking (heart rate controlled at 40–50% of HRR), 20 min of target intensity running, and 5 min of cold walking and dynamic stretching. The training time will be fixed at 17:00–18:30 every day to reduce the impacts of circadian factors. The dual-track “check-in + sports data upload” system will be used to supervise the activity, and participants will wear sports bracelets to record running distance, pace, and heart rate data. These data will be submitted weekly. Compliance is defined as an attendance rate ≥80% (≥9 sessions completed over 4 weeks). Participants with attendance < 80% will not be excluded from the intention-to-treat (ITT) analysis but will be excluded from the per-protocol (PP) analysis.

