#### Tai Chi group

The simplified 24-style Tai Chi will be used as a second intervention exercise as it is concise and easy to master by novices while retaining the core essentials of traditional Tai Chi. It consists of 24 movements, such as “starting momentum”, “wild horse mane”, and “white crane wings”, with a drill duration of about 8–10 min, and a total session duration of about 30 min including warm-up, practice, and the closing posture of Tai Chi. Training will be delivered 3 times per week at 17:00–18:30 both for convenience and temporal consistency with the other interventions. Each training session will be divided into three phases: a 5-min warm-up (including neck rotation, joint movement, lunge leg press), 20-min Tai Chi routine practice (including two repetitions), and the 5-min closing (pranayama relaxation, tapping the meridians). The selected Tai Chi training intensity aims for “slight sweating, steady breathing, and consistent movements”, and will be monitored by the Subjective Fatigue Scale (RPE), which requires the participants to maintain an RPE score of 11–13 (slightly tired but sustainable) during the training. At the same time, participants will use a wearable device to ensure that average heart rate remains at 50–65% of HRmax. The Tai Chi intervention will adopt “online + offline” dual supervision. During offline training, the coach will observe the participants' movements on video submitted via an online video application, from which the coach will provide remote guidance. Attendance will be summarized monthly. Compliance is defined as an attendance rate ≥80% (≥9 sessions completed over 4 weeks); if attendance is < 80%, reasons will be documented and participants will be encouraged to improve, with reasons recorded for sensitivity analysis.

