### Data management and monitoring

Outcome measures, adverse events, and safety assessment data will be recorded systematically at indicated timepoints on case report forms (CRFs). A dedicated outcome evaluator will ensure the timeliness, accuracy, and completeness of data entry in accordance with requirements of the International Common Reporting Format (ICH-GCP E3/E6 standard). All paper and electronic records will be kept for at least 5 years after the end of the study to meet the traceability requirements of regulatory agencies. The anonymized trial data will be available to peer researchers for at least 3 years after the publication of the first main article, but a patient privacy protection protocol will be strictly implemented throughout, and all personally identifiable information (including name, ID number, contact number, etc.) will be encoded and encrypted to ensure that the data can be desensitized before it can be included in the analysis. The research protocol presented here has been independently reviewed and optimized by experts in the fields of acupuncture, emergency medicine, methodology, and biostatistics to ensure scientific and ethical integrity. The Institutional Ethics Committee (IEC) of the Third Affiliated Hospital of Henan University of Traditional Chinese Medicine will conduct annual on-site verification and data quality assessment independently of the investigators and the sponsor, and any changes in operating procedures shall be recorded on a Protocol Deviation Report Form and submitted to the Ethics Committee and the China Clinical Trial Registry for filing and review.

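### The adverse-event section and its dedicated form are written for acupuncture only, so harms would be ascertained unequally across the three arms

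*Protocol article*

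**What the plan says.** The Adverse events section of the protocol article is the only section devoted to harms. It begins "Adverse events that may occur during acupuncture include broken, syncope, local hematoma, infection, and abscess" and continues that "post-acupuncture discomforts may include residual acupoint site pain, nausea, vomiting, palpitations, dizziness, headache, anorexia, and insomnia". It stresses prompt recording, and then states that "the incidence rates and average frequencies of these events will be recoded on a specific form for review and appropriate follow-up". The only events named before that sentence are those two acupuncture lists.

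Other sections are wider:

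- Dropout criteria includes "Serious adverse reactions to the interventions", in the plural and with no arm named.
- The handling of dropped cases provides that "For cases that quit the trial due to adverse reactions or ineffective treatment, the attending doctor will take appropriate measures", again for any arm.
- Data management and monitoring says that "Outcome measures, adverse events, and safety assessment data will be recorded systematically at indicated timepoints on case report forms (CRFs"), also without an arm limit.

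No section lists anticipated harms of running or Tai Chi. The Running group section plans a baseline treadmill test with escalating load (Bruce protocol) and training at 60–75% of heart rate reserve.

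**The concern.** The trial randomises students to three active interventions, and the Discussion already describes these as safe. The section that sets up harm recording is written as if only acupuncture could cause harm. If staff follow it literally, a participant in the acupuncture arm is assessed against a named list on a dedicated form that leads to review and follow-up. A runner or Tai Chi participant is covered by the general case report form and nothing more specific.

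Two things are at stake. The first is participant safety: the promised review is attached, as written, to acupuncture events. The second is interpretation: events that are asked about are generally reported more often than events left to general reporting, so a table of events by arm would mix true differences with differences in how hard each arm was asked. The likely direction is against acupuncture, the intervention the trial mainly sets out to evaluate.

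**Working it through.** This is mainly a matter of reading passages side by side. The arithmetic only sets the scale.

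**Share of participants affected.** Inputs are from Sample size: 27 per group, about 10% dropout, 30 per group.
- Plan's own figure: 27 / (1 − 0.10) = 30 per group, and 3 × 30 = 90. This reproduces.
- Exercise arms: 30 + 30 = 60, and 60 / 90 = 66.7% of randomised participants. The 30 healthy controls receive no intervention and are left out.

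**Share of sessions affected.** Inputs are from Study setting: 3 sessions per week for 4 weeks.
- 3 × 4 = 12 sessions per participant.
- Exercise arms: 12 × 60 = 720. All arms: 12 × 90 = 1,080.

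**What the list contains.** Inputs are from Adverse events.
- During acupuncture: 5 items. After acupuncture: 8 items. Total 5 + 8 = 13, all introduced as acupuncture events.
- Specific to needling or its site: the broken item (presumably a needle), hematoma, infection, abscess and acupoint pain = 5.
- Non-specific symptoms that could occur in any arm: syncope, nausea, vomiting, palpitations, dizziness, headache, anorexia and insomnia = 8.
- Falls, strains or other musculoskeletal injuries: 0.

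So even if the list were applied unchanged in every arm, it would prompt for 8 symptoms relevant to exercise and for no exercise injury.

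**Scope, section against section.**

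| Section | Arms covered as written | What it provides |
|---|---|---|
| Adverse events | Acupuncture | Named list, dedicated form, review and follow-up |
| Data management and monitoring | Not limited | General recording on case report forms at unspecified timepoints |
| Dropout criteria | All interventions | Serious reactions as a reason for dropout |
| Handling of dropped cases | Not limited | Action by the attending doctor once a participant has quit |

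The last three rows presuppose that harms are identified in every arm. The first row sets up the active means of identifying them for one arm. The wider provisions do not close the gap: the dropout provisions concern serious reactions or participants who leave, and the general case report form comes with no list.

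**Contact with staff.** Needling requires a practitioner at each session. For running, the plan describes check-in, real-time heart-rate monitoring and bracelet data on distance, pace and heart rate, of which it says "These data will be submitted weekly". For Tai Chi, supervision combines online and offline elements, with a fatigue scale and a wearable device; in part, "the coach will observe the participants' movements on video submitted via an online video application, from which the coach will provide remote guidance". Neither exercise section describes a symptom or injury question. This could add to the imbalance, but the text does not allow it to be measured.

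**The case against.** The strongest reply is that harms in the exercise arms are recorded. Data management and monitoring covers adverse events with no arm limit, and the dropout provisions apply to every intervention. The acupuncture lists are introduced as things that may happen, so they can be read as examples, and 8 of the 13 items could be noted in a runner. No between-arm safety comparison appears among the objectives, outcomes or analyses. A journal article also commonly leaves the layout of an adverse-event form to the full protocol.

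Much of this stands, and it rules out several stronger readings that a reader might infer:

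- *That only acupuncture harms are recorded, or that the exercise arms would look free of harm by construction.* The general case report form contradicts both.
- *That safety cannot be compared between arms at all.* Events from all arms would exist. They would be collected with unequal intensity.
- *That exercise harms are recorded only at weeks 0, 2 and 4.* Those are the outcome assessment times. The timepoints for adverse events are not stated, and the figures with the schedule and trial scheme are not shown, so no recall interval can be derived.

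What does not stand is the appeal to condensation. The article does not leave the scope of the dedicated form to another document. It states a scope, and states it more narrowly than its own other sections require. Nor does the lack of a formal safety comparison remove the problem: event counts by arm would still be read side by side, and participant safety does not depend on a planned test.

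**Conclusion.** The point holds as one of inconsistent scope and unequal ascertainment. The Adverse events section ties its list, its form and the resulting review to acupuncture, while three other sections imply collection in every arm. As written, 60 of 90 randomised participants (66.7%) and 720 of 1,080 scheduled sessions fall outside the prompted list, which contains no fall or musculoskeletal item.

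The conclusion rests on the plain reading that the form covers the events just listed, and on the general expectation that prompted events are reported more often. The documents give no adverse-event rates, so neither the size of the distortion nor an expected count per arm can be given. The primary efficacy analysis is not affected. The wording should still be corrected before data collection, because events not asked about during the four weeks cannot be reliably recovered later.

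**What to change.** In the Adverse events section:

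1. Extend the recording sentence from the listed acupuncture events to any adverse event in any arm, so that it agrees with Dropout criteria, the handling of dropped cases, and Data management and monitoring.
2. Use one common form and one collection schedule for all three arms. Keep the needling items and add exercise-related ones such as falls, strains and exertional symptoms. Include events at the baseline treadmill test.
3. Have the form completed by people other than the blinded outcome assessors, for example the intervention staff, or through the existing check-in and upload. Needling items seen by an assessor could reveal the allocation, and the Blinding section relies on assessors not knowing it.
4. Report events by randomised arm.

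The cost is a revised form and slightly more data entry. If the form were completed at every session, the upper limit would be 1,080 short entries. A sparser schedule would need fewer, provided that it is the same in each arm. No treatment rule, outcome or sample size changes.

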**Figure 3 F3:**
[figure not shown]
Schematic of the trial protocol. The primary outcome measure will be the GPS and secondary outcome measures will include the PASS. In addition to baseline, intervention, and immediate post- intervention measures, follow-up will be conducted in the first and second weeks after completion of the treatment plan.

### Follow-up

Follow-up will be conducted in the first and second weeks after completion of the treatment plan (Figure 2).

#### Sample size

Sample size estimation was informed by pilot data and by consideration of realistic and conservative effect size assumptions appropriate for behavioral intervention studies. In a pilot study, post-intervention General Procrastination Scale (GPS) scores were 32.5 ± 6.8 in the acupuncture group, 38.2 ± 7.2 in the running group, and 41.6 ± 6.5 in the Tai Chi group after 8 weeks of intervention. Importantly, similar between-group trends were already observable at 4 weeks, supporting the feasibility of a 4-week intervention in the present trial.

However, given the exploratory nature of the current study and the risk of overestimating effects based on pilot data, sample size calculation for the main trial was performed assuming a conservative medium-to-large effect size. Using G^*^Power 3.1, a one-way analysis of variance (ANOVA) design with three intervention groups was specified, with a two-sided significance level of α = 0.05 and statistical power (1–β) = 0.90. An effect size of Cohen's *f* = 0.40 was selected, consistent with effect sizes commonly reported in behavioral and non-pharmacological intervention studies targeting self-regulation and cognitive control outcomes.

Under these assumptions, the required sample size was estimated to be 27 participants per group. Allowing for an anticipated dropout rate of approximately 10%, the final target sample size was set at 30 participants per intervention group, resulting in a total of 90 participants with high procrastination tendencies. In addition, 30 healthy control participants without procrastination will be recruited to provide normative behavioral and electrophysiological reference values.

### Data management and monitoring

Outcome measures, adverse events, and safety assessment data will be recorded systematically at indicated timepoints on case report forms (CRFs). A dedicated outcome evaluator will ensure the timeliness, accuracy, and completeness of data entry in accordance with requirements of the International Common Reporting Format (ICH-GCP E3/E6 standard). All paper and electronic records will be kept for at least 5 years after the end of the study to meet the traceability requirements of regulatory agencies. The anonymized trial data will be available to peer researchers for at least 3 years after the publication of the first main article, but a patient privacy protection protocol will be strictly implemented throughout, and all personally identifiable information (including name, ID number, contact number, etc.) will be encoded and encrypted to ensure that the data can be desensitized before it can be included in the analysis. The research protocol presented here has been independently reviewed and optimized by experts in the fields of acupuncture, emergency medicine, methodology, and biostatistics to ensure scientific and ethical integrity. The Institutional Ethics Committee (IEC) of the Third Affiliated Hospital of Henan University of Traditional Chinese Medicine will conduct annual on-site verification and data quality assessment independently of the investigators and the sponsor, and any changes in operating procedures shall be recorded on a Protocol Deviation Report Form and submitted to the Ethics Committee and the China Clinical Trial Registry for filing and review.

